## Abstract

**Background:**

Syndesmotic injuries are common and their incidence is rising. In case of surgical fixation of the syndesmosis a metal syndesmotic screw is used most often. It is however unclear whether this screw needs to be removed routinely after the syndesmosis has healed. Traditionally the screw is removed after six to 12 weeks as it is thought to hamper ankle functional and to be a source of pain. Some studies however suggest this is only the case in a minority of patients. We therefore aim to investigate the effect of retaining the syndesmotic screw on functional outcome.

**Design:**

This is a pragmatic international multicentre randomised controlled trial in patients with an acute syndesmotic injury for which a metallic syndesmotic screw was placed. Patients will be randomised to either routine removal of the syndesmotic screw or removal on demand. Primary outcome is functional recovery at 12 months measured with the Olerud-Molander Score. Secondary outcomes are quality of life, pain and costs. In total 194 patients will be needed to demonstrate non-inferiority between the two interventions at 80% power and a significance level of 0.025 including 15% loss to follow-up.

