### Sample size

We based our sample size calculation on a non-inferiority design. The Olerud-Molander score (OMAS) will serve as primary outcome measure. We have used the results from an earlier study on this subject for our sample size calculation [27]. For the sample size calculation we hypothesized an equal OMAS between the two groups. Using a one-sided significance level (α) of 0.025 and a power (ß) of 90% with a standard deviation (SD) of 19 points (derived from the study mentioned before) and setting our non-inferiority limit at 10 a total of 76 patients are needed in each study arm. Taking a 10% loss to follow-up into account, a total number of 167 subjects will be needed to demonstrate non-inferiority between the two treatment strategies. Furthermore we performed a sample size calculation for a subgroup analysis based on age. We hypothesize that the SD will be lower in these subgroups due to increased homogeneity, therefore we have used an SD of 16 for the sample size calculation of the subgroups. Using a significance level (α) of 0.05 and a power (ß) of 90% 88 patients are needed in each subgroup to prove non-inferiority. Taking 10% loss to follow-up into account a total of 193 patients need to be randomized.

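### The abstract's sample-size statement (194 patients, 80% power, 15% loss) contradicts the Sample size section and is wrong for the primary comparison on the protocol's own inputs

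*Protocol article*

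**What the plan says.** The Design paragraph of the abstract ties 194 patients to the comparison of the two interventions, "at 80% power and a significance level of 0.025 including 15% loss to follow-up". It gives no SD and no margin, and does not mention age subgroups.

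The Sample size section makes two calculations.

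- **Primary comparison.** It assumes no true difference ("For the sample size calculation we hypothesized an equal OMAS between the two groups"), a one-sided alpha of 0.025, "a power (ß) of 90% with a standard deviation (SD) of 19 points", and a margin of 10: "setting our non-inferiority limit at 10 a total of 76 patients are needed in each study arm". With 10% loss, "a total number of 167 subjects will be needed to demonstrate non-inferiority between the two treatment strategies".
- **Age subgroups.** It uses SD 16, alpha 0.05 with no sidedness given, and 90% power, and arrives at 88 patients per subgroup. "Taking 10% loss to follow-up into account a total of 193 patients need to be randomized".

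The Statistical analysis section confirms the one-sided 0.025 for the primary test. It allows a claim of non-inferiority only if the intention-to-treat and per-protocol analyses both show it.

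**The concern.** Power, loss allowance and total all differ between the abstract and the Sample size section: 80% against 90%, 15% against 10%, and 194 against 167 for the same comparison (or 193 for the trial). Both sets are stated outright as current text, so condensation into an article does not explain the difference.

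These are the figures against which the completed trial will be judged. As written, a reader cannot tell what attrition was planned for. A reader of the abstract alone would take 194 to be the minimum for 80% power on the primary outcome, and would not learn that a subgroup calculation sets the total. The loss rate also matters for the subgroup target. The section needs 2 × 88 = 176 evaluable patients for its subgroups, and 193 randomised with 15% loss would leave only about 164.

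**Working it through.** **Inputs.** From the Sample size section: margin 10, true difference 0; primary SD 19, one-sided alpha 0.025, power 90%, loss 10%; subgroup SD 16, alpha 0.05, power 90%, loss 10%. From the abstract: N 194, power 80%, alpha 0.025, loss 15%. Allocation is 1:1 (Interventions section).

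**Formulas** (normal approximation).

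- n per arm = 2 × SD² × (z_α + z_β)² / margin²
- power = Φ(margin / (SD × √(2/n)) − z_α)
- number to randomise = evaluable number / (1 − loss)

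**1. The section's own figures reproduce before loss is added.**

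- Primary: 2 × 361 × (1.960 + 1.282)² / 100 = 75.9, so 76 per arm and 152 in total.
- Subgroups: 2 × 256 × (1.645 + 1.282)² / 100 = 43.8, so 44 per arm and 88 per subgroup, 176 in all. This requires alpha 0.05 to be one-sided. At one-sided 0.025 the result is 53.8, so 54 per arm and 108 per subgroup.

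**2. The abstract's terms applied to the primary comparison.**

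- 2 × 361 × (1.960 + 0.842)² / 100 = 56.7, so 57 per arm and 114 in total.
- 114 / 0.85 = 134.1, so 135. The abstract states 194.

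**3. Power of the primary comparison at the stated totals** (SD 19, margin 10, one-sided 0.025, one analysis).

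| Randomised | Loss | Evaluable per arm | Power |
|---|---|---|---|
| 167 | 10% | 75.15 | 89.7% |
| 193 | 10% | 86.85 | 93.4% |
| 194 | 15% | 82.45 | 92.2% |

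The noncentral t distribution gives 89.4%, 93.2% and 91.9%, so the approximation does not affect the conclusion.

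**4. Where 194 might come from.** Two routes reach it.

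- A subgroup calculation on the abstract's terms with SD 16 and margin 10: 2 × 256 × (1.960 + 0.842)² / 100 = 40.2, so 41 per arm and 82 per subgroup. Then 82 / 0.85 = 96.5, so 97 per subgroup and 194 in total.
- The section's own subgroup total: 176 × 1.10 = 193.6, which rounds up to 194 (the section rounds down to 193).

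The first route borrows SD 16 and margin 10 from the Sample size section, because the abstract gives neither. The document does not show which route was used.

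**5. The loss allowance in the Sample size section.**

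- 152 × 1.10 = 167.2 and 176 × 1.10 = 193.6 match the stated 167 and 193, both rounded down.
- Dividing by 0.90 gives 168.9, so 169, and 195.6, so 196.
- At 10% loss, 167 leaves 150 evaluable (152 needed) and 193 leaves about 174 (176 needed).
- With 193 split equally over the subgroups there are 193 × 0.90 / 4 = 43.4 per arm. Subgroup power is then Φ(10 / (16 × √(2/43.4)) − 1.645) = Φ(1.267), also just under 90%.

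**The case against.** The strongest reply is that nothing important turns on this. The two totals to randomise differ by one patient. The primary alpha agrees in the abstract, the Sample size section and the Statistical analysis section. The margin, test and decision rule are untouched. Under either set of figures the primary comparison exceeds its stated power, so the abstract errs on the cautious side. All of that stands, and it limits the point to a correction of stated figures. It does not remove the contradiction, and it does not make 80% the power of the comparison that the abstract names.

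Three stronger readings are tempting and are not supported.

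- A reader might infer that neither 80% nor 90% is the power of the primary comparison. But 90% is its correct design power at 76 per arm (90.05% by the formula). The total of 193, set by the subgroups, merely takes the power above it.
- A reader might infer that the abstract's 194 can only be a subgroup calculation presented as the primary one. That is possible, but rounding 193.6 up also gives 194.
- A reader might treat the loss formula as a serious error. It costs 2 or 3 patients and leaves power at 167 at 89.7%. With 193 randomised, the shortfall at 167 never arises for the primary comparison: about 174 would be evaluable against 152 needed. It has no demonstrated bearing on the abstract's figures.

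**Conclusion.** The point holds as a contradiction and as a wrong statement in the abstract. For the primary comparison, 80% power with 15% loss corresponds to 135 patients, and 194 patients with 15% loss correspond to about 92% power. The multiplication by 1.10 is a genuine but minor slip of 2 and 3 patients.

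The trial is not underpowered for its primary comparison on these inputs. The power figures rest on SD 19, margin 10, no true difference, equal arms and the stated loss rates, and each refers to one analysis. Because intention-to-treat and per-protocol must both succeed, the joint probability of success cannot exceed that of either analysis, and it may be lower if per-protocol exclusions shrink the set. The documents give no exclusion rate from which to compute it.

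**What to change.** - The sponsor states which loss rate was planned, 10% or 15%. The documents do not favour either.
- Use one set of N, power, alpha and loss in the abstract and the Sample size section.
- Say in both places that the age-subgroup calculation drives the total, and give its alpha, sidedness and power.
- Report the resulting power of the primary comparison: about 93% at 193 with 10% loss, or about 92% at 194 with 15% loss. Label it as the power of a single analysis, and note that the requirement for both intention-to-treat and per-protocol success can make the joint power lower.
- If 10% loss stays, either correct 167 and 193 to 169 and 196, or keep the totals and state the evaluable numbers (about 150 and 174) with power just under 90%. If 15% is adopted with the section's subgroup inputs, 176 / 0.85 = 207.1, so 208 would be needed to keep 176 evaluable; otherwise the subgroup power should be restated.

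The cost is a change of wording and numbers. The primary comparison needs no extra patients. Only the subgroup target could call for more, and restating its power avoids that.

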**Discussion:**

If removal on demand of the syndesmotic screw is non-inferior to routine removal in terms of functional outcome, this will offer a strong argument to adopt this as standard practice of care. This means that patients will not have to undergo a secondary procedure, leading to less complications and subsequent lower costs.

**Trial registration:**

This study was registered at the Netherlands Trial Register (NTR5965), Clinicaltrials.gov (NCT02896998) on July 15th 2016.

## Background

Ankle fractures are among the most common fractures. It is estimated that the incidence of ankle fractures ranges from about 25,000 in the Netherlands to more than five million people in the United States annually and the incidence is rising [1, 2]. Both young and elderly people are at risk for these fractures. In general, younger people are more at risk as a result of a more active lifestyle and elderly people because of poorer bone quality [3, 4]. Approximately half of the patients with an ankle fracture require surgical treatment because of joint instability. In approximately 20% of these fractures there is a concomitant injury of the syndesmosis and syndesmotic repair is indicated [5]. After anatomical reduction a syndesmotic ‘positioning screw’ is placed through the fibula into the tibia to maintain this reduction and allow the syndesmotic ligaments to heal. Extensive research has been conducted regarding the technical aspects of the placement of the syndesmotic screw. For example, the number of screws, their diameter, the level of placement and whether they should engage three or four cortices have been investigated thoroughly [6–10]. After a period of 8 – 10 weeks the syndesmosis will generally be healed and the screw will lose its function. It is an ongoing discussion whether the syndesmotic screw needs to be removed subsequently. Most surgeons advocate its removal because of suspected impaired range of motion and chance of breakage of the screw [9, 11–13]. During normal ambulation the fibula moves and the syndesmosis widens [14, 15]. The positioning screw is thought to restrict this movement and the screw is therefore removed. However, several case series have shown similar outcomes in patients in which the syndesmotic screw was retained compared to patients in whom the syndesmotic screw was removed [16–18]. The positioning screw is most likely not causing complaints in patients with retained screws because of loosening or breakage of the screw [16, 17, 19, 20]. In a recent systematic review there seemed to be no significant difference in functional outcome between patients undergoing routine removal and patients in whom the syndesmotic screw was only removed in case of symptomatic implants. [21] However, this was only based on one underpowered RCT and several low quality case-series and therefore high-quality evidence on this subject is desirable.

We therefore initiated a randomized controlled trial in which we aim to investigate the effect of ‘removal of demand’ of the syndesmotic screw(s) compared to ‘routine removal’ on functional outcome. Furthermore we will investigate the economic effect of leaving the syndesmotic screw(s) in place.

### Design

This pragmatic international multicentre randomised controlled trial will randomise between routine- and on demand removal of the syndesmotic screw(s) after placement for a traumatic syndesmotic injury (both isolated syndesmotic injuries and concomitant syndesmotic injuries in ankle fractures). Both teaching and non-teaching hospitals will participate in this study including three academic Level 1 trauma centres in Europe. An overview of participating centres is shown in Table 1.

**Table 1 Tab1:** Participating centres

Academic Medical Centre^a^	Amsterdam, the Netherlands
Bovenij Hospital	Amsterdam, the Netherlands
Catharina Hospital	Eindhoven, the Netherlands
Deventer Hospital	Deventer, the Netherlands
Flevo Hospital	Almere, the Netherlands
Haaglanden MC	The Hague, the Netherlands
Helsinki University Hospital^a^	Helsinki, Finland
Jeroen Bosch Hospital	‘s-Hertogenbosch, the Netherlands
Maasstad Hospital	Rotterdam, the Netherlands
Noordwest Hospital Group	Alkmaar, the Netherlands
OLVG	Amsterdam, the Netherlands
Slotervaart Hospital	Amsterdam, the Netherlands
Spaarne Hospital	Amsterdam, the Netherlands
VU University Medical Centre^a^	Amsterdam, the Netherlands
Westfries Hospital	Hoorn, the Netherlands

^a^level 1 trauma centres

### Participants

The eligible study population will consist of consecutive adult patients with a traumatic syndesmotic injury.

### Inclusion criteria

Placement of one or two metallic syndesmotic screw(s) for an unstable ankle fracture with a syndesmotic injury or an isolated syndesmotic injurySyndesmotic screw(s) placed within 2 weeks of the traumaPhysical condition allows the patient to undergo an elective second procedure (i.e. removal of the screw)

### Exclusion criteria

ISS score > 15Injuries to the ipsi- and contralateral side which may hamper rehabilitationOther medical conditions which hamper physical rehabilitation (i.e. musculoskeletal disabilities or severe psychological conditions)Insufficient understanding of the Dutch or English language

### Interventions

Patients will be informed about the study by their treating physician following the procedure in which the syndesmotic screw was placed. After this, patients are contacted by the coordinating investigator to request participation in the study. After obtaining signed informed consent patients will be randomly assigned in a 1:1 allocation ratio to one of the following groups:Control group: Routine removal of the syndesmotic screw(s) 8 – 12 weeks following the index procedureor2)Intervention group: On demand removal of the syndesmotic screw(s)

Patients in the control group will undergo routine removal of the syndesmotic screw 8 – 12 weeks post-operatively (according to the preference of the treating surgeon). Patients will not undergo routine removal in case of 1) a contra-indication for undergoing a second procedure for example due to a (new) medical condition or 2) explicit request of the patient after consultation of their treating surgeon. In the intervention group the screw will only be removed in case of symptomatic implants, defined as: 1) implants causing pain, 2) implants (suspected of) causing restricted range-of-motion 3) explicit request of the patient 4) an infection or 5) other problems related to the screw such as protruding screw-head. The screw will only be removed after a consultation of the treating surgeon (except in patients who wish to no longer participate in the study). In patients in the control group in whom the syndesmotic screw brakes prior to planned removal, the screw will be left in place and only removed in case of symptoms.

### Study procedures

This study is a pragmatic trial, which implies physicians are allowed to follow local guidelines concerning the treatment of these injuries apart from the intervention investigated. Participating centres are however informed that the preferred surgical technique is a tricortical 3.5 mm diameter screw between 2 and 4 cm of the pilon. If a large reduction clamp is used, the preferred technique is the use of a temporary K-wire as ‘glide path’ [22]. Besides this, participating centres are allowed to choose their own postoperative treatment routine: for example in the use of a cast, non-weight bearing regime and timing of syndesmotic screw removal (within the predefined time window). At 3 months following the index procedure, patients are assessed at the outpatient clinic. Patients are instructed to visit the outpatient clinic sooner in case of any signs of a POWI: warmth, redness, pain, drainage or a fever above 38.5 degrees Celsius. During the visit to the outpatient clinic the patients are seen by their treating physician and the coordinating investigator. The coordinating investigator will document signs of POWI and will determine its presence or any special findings on physical examination. Furthermore patients are requested to fill out several questionnaires (Table 1). At the six and 12 months follow-up, patients are requested to fill out the same questionnaires and the range-of-motion is measured. Follow-up will take place within a window of 2 weeks of the projected follow-up moment.

### Randomisation

Randomisation will be stratified by centre and age category (i.e. ≥ 60 years and < 60 years). Randomisation will be blocked within strata. Randomisation sequence is generated by a dedicated computer randomisation software program (CASTOR®, Amsterdam, The Netherlands), ensuring allocation concealment. Randomisation will mostly be performed at the outpatient clinic by coordinating investigator using a dedicated, password protected, SSL–encrypted website.

### Primary Outcome

The primary outcome parameter is functional outcome 12 months following the index procedure measured with the Olerud-Molander ankle score (OMAS) (Table 2).

**Table 2 Tab2:** Time table and follow-up schedule

RODEO-trial	Enrollment	Randomization / Allocation	Follow-up		
TIMEPOINT	Post-operatively	8 – 12 weeks post-operatively	3 months Post-operatively	6 months Post-operatively	12 months Post-operatively
Enrollment					
Eligibility screening	X				
Informed Consent	X				
Intervention					
Removal of syndesmotic screw (according to randomization)		X			
Assessment					
Plain radiographs	X		X		
OMAS			X	X	X
Visual analogue pain scale (VAS)			X	X	X
Range-of-Motion			X	X	X
POWI			X		
AOFAS			X	X	X
EQ-5D-5 L			X	X	X
i-MCQ			X	X	X
i-PCQ			X	X	X

To be able to assess the Minimally Clinical Important Difference of the OMAS, anchor questions will be added to the OMAS at six and 12 months as described by Walenkamp et al. [23].

### Secondary outcomes

#### Secondary outcome measures of the study are:

Functional outcome with the American Orthopedic Foot and Ankle Hindfoot Score (AOFAS) [24]Pain as measured by a ten-point Visual Analog Scale.Range of motion, both absolute and as a percentage compared with the uninjured side.Postoperative wound infections classified using the criteria as defined by The Centers for Disease Control and Prevention (CDC-criteria) [25]Synostosis or recurrent diastasis (as seen on radiographs made in case of symptoms)Health-related quality of life as measured by the EQ-5D-5 L questionnaire [26].Health care resources utilization (including amongst others; number of visits to the general practitioner and use of home care organizations) as measured by way of a combination of the Dutch/English iMTA Medical Consumption Questionnaire (iMCQ) and iMTA Productivity Cost Questionnaire (iPCQ) (only applicable for the Dutch study population).Costs (economic evaluation including budget impact analysis): the economic evaluation of the RODEO-trial will be performed as a cost-effectiveness (CEA) as well as a cost-utility (CUA) analysis (only applicable for the Dutch study population).

Furthermore general demographics will be assessed such as age, gender, body mass index, co-morbidities, American Society of Anesthesiologists (ASA) classification, substance abuse, level of activity, bone mineral density (when available), fracture characteristics, surgical characteristics, duration of non-weight bearing period and use of physiotherapy.

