### Statistical analysis

The primary endpoint will be analysed according to the intention-to-treat and the per-protocol principle, non-inferiority will only be declared if both types of analysis prove non-inferiority. The primary endpoint will be analysed using a one sided test for non-inferiority with an alpha of 0.025. Descriptive methods will be used to assess quality of data, homogeneity of treatment groups and endpoints. Normality of the data will be analysed by visually inspecting the histograms. Secondary outcomes will be analysed using either a t-test or Mann-Whitney U test for continuous data according to the distributing of the data and a Chi Square test for categorical data. Missing data will be handled through multiple imputation with predictive mean matching. All analyses will be performed using the standard statistical software. Separate analyses will be performed on subgroups based on age. A multivariable analysis will be performed to identify predictors of worse functional outcome.

The CEA and CUA will be performed on the intention to treat data, with a time horizon of 12 months and from a societal perspective. The primary economic outcomes are the costs per quality adjusted life year (QALY) and the costs per point functional recovery improvement. Moreover a budget impact analysis (BIA) will be performed with a time horizon of 4 years. The questionnaires estimating the secondary outcome measures ‘resources utilization’ and ‘costs’ will only be used in patients included in the Netherlands due to practical feasibility and to ensure a valid outcome.

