### Benefits and risks assessment, group relatedness

A recent systematic review suggests that our intervention is safe and has similar functional outcome compared to the routine removal [21]. Subjects will not undergo additional investigations and interventions due to participation in the RODEO-trial and therefore risks to subjects involved in this trial are at least similar to current practice. Potential benefits for subjects in the investigational treatment arm could be a lower risk of surgical site infections and not having to undergo a secondary procedure.

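### Synostosis and recurrent diastasis are counted only on symptom-triggered films, although Table 2 schedules plain radiographs at 3 months with no symptom condition (minor; one secondary outcome)

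*Protocol article*

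**What the plan says.** In the protocol article, the list under Secondary outcomes contains "Synostosis or recurrent diastasis (as seen on radiographs made in case of symptoms". Only films prompted by complaints therefore contribute to this outcome.

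Table 2 (follow-up schedule, under Primary Outcome) has a row "Plain radiographs" with a mark post-operatively and a mark at 3 months. There is none at 6 or 12 months, and no note limits the row to patients with symptoms. Under Study procedures, "At 3 months following the index procedure, patients are assessed at the outpatient clinic"; that text does not mention films.

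Under Interventions, controls have routine removal at 8 to 12 weeks, whereas "In the intervention group the screw will only be removed in case of symptomatic implants", and "The screw will only be removed after a consultation of the treating surgeon". The section on benefits and risks states that "Subjects will not undergo additional investigations and interventions due to participation in the RODEO-trial". Under Statistical analysis, the between-arm comparison of a categorical secondary outcome is "a Chi Square test for categorical data".

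**The concern.** An outcome seen only on a radiograph is compared fairly between arms when the chance of having that radiograph is the same in both. Here the film depends on symptoms. Pain and suspected restricted motion are also reasons for removing the screw in the on-demand arm, so complaints there have a consequence that they do not have for a control whose removal is already planned. No blinding is described, and patients and treating surgeons necessarily know whether removal was planned. Imaging for symptoms could therefore differ by arm even if the structural event rate does not.

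Asymptomatic cases that a scheduled 3-month film would show also go uncounted under the definition as written.

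What is at stake is the reading of one complication outcome. It has some weight because the Abstract and the Discussion both say that adopting on-demand removal would lead to fewer complications. The OMAS comparison and the non-inferiority decision do not depend on it.

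**Working it through.** **Plan's own figure.** The article gives no rate, power or sample size for this outcome, so there is nothing to reproduce. The check compares passages and adds an illustration on assumed inputs.

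**Step 1: definition against schedule.**
- Secondary outcomes: films made because of symptoms count.
- Table 2: films post-operatively and at 3 months, marked in the same way as OMAS and VAS, which apply to everyone.
- The natural reading is that each patient has a post-operative and a 3-month film, and that the outcome definition does not use the latter unless it was prompted by symptoms. The table does not say in words that every patient is imaged.

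**Step 2: when the 3-month film falls.**
- Removal in controls: 8 to 12 weeks after the index procedure (Interventions).
- Visit: 3 months = 52/4 = 13 weeks. Follow-up is within a 2-week window (Study procedures); read as plus or minus 2 weeks, this is 13 − 2 = 11 to 13 + 2 = 15 weeks.
- Film relative to removal: from 11 − 12 = −1 week (before removal) to 15 − 8 = 7 weeks (after removal).

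The film removes dependence on symptoms for events visible by then. It leaves little or no time for a recurrence that follows removal, and nothing later is scheduled.

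**Step 3: what unequal imaging could do (assumed inputs).** With an equal true rate p in both arms and a detection probability d in each arm, observed rate = p × d, and the observed ratio is the ratio of the two values of d.
- Evaluable per arm, from the Sample size section and "patients will be randomly assigned in a 1:1 allocation ratio": 193 × 0.90 / 2 = 86.85, about 87.
- Assume p = 10%, and d = 30% in one arm and 15% in the other, with imaging unrelated to the finding. Observed rates: 0.10 × 0.30 = 3.0% and 0.10 × 0.15 = 1.5%, a ratio of 2.0 where the truth is 1.0.
- Expected patients: 87 × 0.030 = 2.6 and 87 × 0.015 = 1.3, a difference of about one.
- Exact chance of a significant chi-square result (two-sided 5%) at these rates: 8.0% uncorrected, 1.5% with continuity correction.
- A wider assumed gap, d = 20% against 40% to 60% at p = 10%, gives ratios of 2.0 to 3.0 on 1.7 against 3.5 to 5.2 expected patients. The chance of a false significant result is then roughly 12% to 27% by a normal approximation, which is crude at such small counts.
- If d is 20% in both arms, the ratio is unbiased (1.0), but 1 − 0.20 = 80% of cases are missed.

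The values of p and d have no source in the documents. The share of cases missed is simply one minus the assumed d. If these complications themselves cause symptoms, imaging is not unrelated to the finding, and the example does not describe the trial.

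**The case against.** The strongest reply is that the two places need not conflict. Table 2 says when films are taken; the outcome definition says which films count. A pragmatic trial may choose to count only symptomatic synostosis or diastasis over 12 months, and the article states that participation adds no investigations. This stands in part: the passages can be made compatible. The article does not say, however, what the scheduled film is for or why it is disregarded, so a clarification is still needed.

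Second, arm-dependent imaging is inferred. The text on consulting the surgeon concerns removal, not radiographs, and both arms have the same planned contacts: the 3-month visit, and questionnaires and range of motion at 6 and 12 months. Controls whose screw breaks before planned removal are also managed by symptoms. This stands. A reader might infer that the protocol shows imaging to differ by arm, or that a two-fold distortion is to be expected; the documents support neither. They support only that detection could differ.

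Third, a reader might infer that the bias is wholly avoidable by moving the outcome to the 3-month film. It is not. That film comes between about a week before and 7 weeks after control removal, so a comparison resting on it alone would lean towards no difference and would give up the coverage to 12 months. This objection stands in full and limits the remedy.

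Finally, film-reading rules may sit in a full protocol or SAP that is not shown. That is fair, and their absence is not criticised here. The point rests on the outcome definition and the table as printed.

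**Conclusion.** The point holds in a limited form. As written, the outcome ignores routine films that Table 2 appears to schedule in both arms and relies on symptom-triggered detection where symptoms are tied to the allocated strategy. The consequences are that asymptomatic cases visible on the scheduled films go uncounted, and that detection may differ by arm in a direction and to a degree that the documents do not allow one to derive. The two-fold ratio is an illustration on assumed rates and should not be quoted as an estimate.

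The conclusion assumes that the unconditional marks in Table 2 mean imaging of all patients. If the 3-month film is in fact taken only for symptoms, the table is what needs correcting, and asymptomatic cases cannot be recovered from it.

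This is a minor point on one of eight listed secondary outcomes. The article does not call it a safety outcome or a main harm, and the primary analysis is untouched.

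**What to change.** 1. Reconcile the outcome definition with Table 2. If the 3-month film is symptom-driven, add that condition to the table.
2. If it is routine, count synostosis or recurrent diastasis on the 3-month film in all patients, compared with the post-operative film, in addition to symptom-triggered films up to 12 months. Where possible, have the films read without knowledge of allocation.
3. Report the two sources separately, each with the number of patients imaged per arm, and describe the symptom-triggered comparison as open to detection bias.
4. Do not let the 3-month film replace the 12-month ascertainment or serve as the only between-arm comparison.

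The cost is the rewording of one outcome, the reading of films already scheduled and one extra line of reporting. No imaging is added, so the change fits the statement that participation brings no additional investigations. Events after 3 months would still be found only through symptoms.
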